### Adverse Events (AEs)

Based on the anticipated severity of the study population informed by recent observational studies in Australian and New Zealand PICUs (7, 11, 41) a proportion of study patients are expected to suffer from complications related to septic shock unrelated to study interventions (42). Major AEs including death, cardiopulmonary arrest, ECMO and amputations will be captured in all patients. In addition, we will report any AE potentially causally related to the study intervention or which is of concern in the investigator's judgement. Specific additional AEs captured include limb ischemia, extravasation injury, hypertension, arrhythmia other than sinus bradycardia or tachycardia, hyperglycaemia, abdominal compartment syndrome, pulmonary edema and confirmed hospital-acquired infection. Adverse events will be assessed routinely until day 28, or until the time of patient discharge from hospital, whichever occurs earlier. The *Data and Safety Monitoring Board (DSMB)* consists of a statistician, an ICU specialist and an emergency specialist will receive regular DSMB reports and immediate access to any serious adverse event reports. The DSMB, once set up, will meet mid-trial and at the completion of the trial.

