#### Hydrocortisone

The dosing schedule is 1 mg/kg/dose (maximum 50 mg per dose) intravenously every 6 h for the duration of study treatment given as a slow bolus.

Study drugs will be given through an existing peripheral or central intravenous line. Drug delivery will occur through dose error reduction software for infusion devices to ensure safe delivery of applied standardized drug concentrations. The dosing is aligned with the ADRENAL steroid treatment regimen (13), and with the protocol for the VITAMIN trial (24) and has been shown to restore serum ascorbic acid concentrations in critically ill patients (34). The study treatment will be given for a maximum of 7 days, until resolution of shock (defined as cessation of inotropes for at least 4 h), discharge from PICU, death, or if major adverse events related to the intervention manifest, whichever occurs first.

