Primary clinical outcome	Survival free of organ dysfunction	• Organ dysfunction defined as pediatric Sequential Organ Failure Assessment (pSOFA) score >0, and will be assessed daily until day 28 while patients are admitted to PICU. Patients dying within 28 days of presentation will be allocated zero days to correct for the competing effect of mortality on duration of organ dysfunction. Patients discharged alive from PICU to the ward or home not requiring ongoing organ support, and not being palliative, will be assumed to have zero organ dysfunction after PICU discharge.
Secondary clinical outcomes	Patient-centred outcomes	• Survival free of inotrope support at 7 days • Survival free of multiorgan dysfunction at 7 days
		• 28-day mortality • Survival free of PICU censored at 28 days • Survival free of AKI censored at 28 days^*^ • PICU length of stay • Hospital length of stay • Functional Status Score and modified Pediatric Overall Performance Category at 28 days • Neurodevelopment, Quality of Life and Functional status 6 months post enrolment
	Proxy measures of intervention efficacy	• Proportion with serum lactate <2 mmol/l at 6, 12, and 24 h post enrolment • Time to normalization of tachycardia during the first 24 h post enrolment^**^ • Time to shock reversal, defined as cessation of inotropes for at least 4 h censored at 28 days

* *Acute Kidney Injury (AKI) will be assessed using serum creatinine levels to classify according to Kidney Disease: Improving Global Outcomes (KDIGO) criteria. Because no baseline creatinine values were available, we applied the age-specific thresholds used in PELOD-2 to define the presumed baseline creatinine values. KDIGO Stage 1 was defined as an increase in creatinine to 1.5 to 1.9 times the presumed baseline; Stage 2 as an increase 2.0 to 2.9 times; and KDIGO 3 as an increase ≥3.0 baseline and/or the use of renal replacement therapy*.

** *Goldstein et al. (35)*.

Long-term follow-up at 6 months post randomization through questionnaire by proxy on validated domains across quality of life (40) and functional status will be investigated and reported separately from the main analyses.

Furthermore, we will determine *proxy measures of intervention efficacy* such as shock reversal, normalization of lactate, and time to reversal of tachycardia [defined by age-specific thresholds for Systemic Inflammatory Response Syndrome (35)].

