### Data Collection

The central study coordination will provide a study booklet for site staff, and perform site visits and regular videoconferencing to ensure high standard study conduct and to discuss any challenges in study progress. The REDCap online database (43), hosted by The University of Queensland, has been setup to capture baseline demographic variables, comorbidities, disease and severity features, pre-defined study outcomes, information on study treatments, and adverse events. The staff at each study site will be trained in completing this electronic case report form (eCRF) and in performing the follow-up questionnaires. Study participants alive at day 28 will be contacted by phone (unless still in hospital) to assess POPC and FSS. Subsequently, the study nurses will contact families ~2 months post randomization by phone to perform the questionnaires by proxy on neurodevelopment, quality of life and functional outcomes–details of the follow-up will be published separately.

Physiological parameters and organ support will be collected upon randomization, then at 1, 6, 12, and 24 h subsequently. We will collect individual components of organ dysfunction and organ support every day until discharged from PICU to calculate pSOFA scores.

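### Routine adverse event assessment ends at hospital discharge if that precedes day 28, so non-fatal events are observed over a window that can differ between arms (minor)

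*Protocol article*

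**What the plan says.** In the protocol article, the section Adverse Events (AEs) sets the rule: routine assessment runs "until day 28, or until the time of patient discharge from hospital, whichever occurs earlier". The same section states "Major AEs including death, cardiopulmonary arrest, ECMO and amputations will be captured in all patients", without giving a time window for those events, and says that any event possibly caused by the intervention, or of concern to the investigator, will be reported. Its list of specific events ends with "abdominal compartment syndrome, pulmonary edema and confirmed hospital-acquired infection".

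Table 2 (Study Outcomes) includes "Hospital length of stay" and "28-day mortality" among the secondary clinical outcomes. Under Data Collection, "Study participants alive at day 28 will be contacted by phone (unless still in hospital) to assess POPC and FSS"; no adverse event question is mentioned for that call. On exposure, the Hydrocortisone subsection says "The study treatment will be given for a maximum of 7 days, until resolution of shock", and it also names PICU discharge, death and major related adverse events as stopping points.

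**The concern.** The end of the safety window is fixed after randomisation by an event that treatment can influence. The Introduction hypothesises faster resolution of shock in the intervention arm, and the trial is open label, so the decision to discharge is made with knowledge of the allocation. If treated children go home sooner, they are watched for less time. With the same true risk, fewer of their non-fatal events would then be recorded.

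The clinical outcomes do not share this feature. Mortality, organ-dysfunction-free survival, PICU-free survival, AKI-free survival and time to shock reversal all run to a fixed 28 days.

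At stake is the safety information that the Sample Size section expects 60 children to provide for the design of a full trial. Non-fatal events between discharge and day 28 are not stated to be routinely sought, although families of surviving children already discharged are to be phoned at day 28.

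**Working it through.** The article gives no figure on this point: no expected stay, no adverse event rate, no timing of events. The recruitment limit in the Sample Size section does not enter. What follows is an illustration on assumed values.

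**Inputs from the article.** Window: the earlier of day 28 or hospital discharge. Allocation 1:1 with 60 children, so about 30 per arm. Study drug for at most 7 days.

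**Assumptions.** The same true 28-day risk P of a non-fatal event in both arms. All children in an arm have the same stay L, with pairs 8 v 10, 8 v 12, 10 v 14 and 7 v 14 days. No event is recorded after discharge.

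**Model A, constant hazard over 28 days.** h = −ln(1 − P)/28, and the observed risk is 1 − exp(−hL). P is set to 10, 20 and 40%.

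- Worked case, P = 20%: h = 0.2231/28 = 0.00797 per day. At 8 days, 1 − exp(−0.0638) = 6.2%. At 12 days, 1 − exp(−0.0956) = 9.1%. The gap is 2.9 points, or 1.85 v 2.74 children of 30.
- Smallest gap, P = 10%, 8 v 10 days: 3.0% v 3.7%, gap 0.7 points (0.89 v 1.11 children of 30).
- Largest gap, P = 40%, 7 v 14 days: 11.99% v 22.54%, gap 10.6 points (3.60 v 6.76 children of 30).

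**Model B, events concentrated early.** A share f of events falls by day 7 and is always seen; the rest is spread evenly over days 7 to 28. Observed risk = P × [f + (1 − f)(L − 7)/21]. P is set to 20 and 40%, and f to 80, 90 and 95%.

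- Smallest gap, P = 20%, f = 95%, 8 v 10 days: 19.0% v 19.1%, gap 0.1 points (0.03 of a child in 30).
- Middle case, P = 20%, f = 80%, 8 v 12 days: 16.2% v 17.0%, gap 0.8 points (0.23 of a child in 30).
- Largest gap, P = 40%, f = 80%, 7 v 14 days: 0.40 × 0.80 = 32.0% v 0.40 × (0.80 + 0.20 × 7/21) = 34.7%, gap 2.7 points (0.80 of a child in 30).

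**With a common 28-day window**, both arms show P under either model and the artefact is zero.

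The timing of events matters most. At the same risk (40%) and the same stays (7 v 14 days), moving from a constant hazard to 80% of events in week one cuts the gap from 10.6 to 2.7 points.

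**The case against.** The case for leaving the rule alone is substantial, and much of it stands.

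- **Deaths.** A reader might infer that late deaths are lost. They are not: 28-day mortality is a fixed-window outcome, and deaths within 28 days also enter the primary clinical outcome.
- **Major and related events.** The cut-off governs what is assessed routinely. Major events are promised for all patients, and possibly related events are to be reported. It would therefore be too strong to say that nothing is collected after discharge. Equally, the promise says who is covered and not for how long, and the discharge-or-day-28 rule is the only time limit given.
- **Timing.** Study drug stops by day 7, or at PICU discharge if earlier. Most listed events belong to acute or inpatient care, and hospital-acquired infection is by name tied to the stay. Fewer such events through a shorter stay is partly a real effect and not an artefact. This makes the early-event model the more credible one.
- **Size.** It is tempting to take the ratio of stays as the bias, for example 10/14 = 0.71, hence 29% fewer counted events. That needs both a constant event rate to day 28 and stays that the article does not give.
- **Analysis.** The Analysis section lists major adverse events separately and specifies no test on them, so no formal comparison is distorted. Even so, readers and the DSMB may compare counts by arm.
- **Full protocol.** The article is condensed, and the full protocol may include adverse event questions in the day-28 call. The window itself, however, is stated here.
- **Parent report.** A phone call cannot establish hyperglycaemia, arrhythmia or pulmonary oedema, and parents know the allocation. This limits the remedy without removing the reason for it.

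**Conclusion.** The point holds as a minor one. Non-fatal adverse events have an outcome-dependent window that can differ by arm and can favour the arm discharged earlier. The documents do not support the stronger reading that the safety comparison is biased in favour of the intervention. That would need a real difference in stay together with non-fatal events after discharge, and the article gives no figures for either.

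On the assumed stays, the artefact lies between 0.7 and 10.6 points under a constant hazard (28-day risk 10 to 40%), and between 0.1 and 2.7 points if 80 to 95% of events occur in the first week (risk 20 to 40%). Given the short exposure and the kind of events listed, the lower range is the more plausible, which is less than one child in an arm of 30. The reason to act is the low cost of closing the gap, not a demonstrated distortion.

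**What to change.** In Adverse Events (AEs), end the assessment window at day 28 for every child, whether or not discharged, and state that this applies to the major events too.

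In Data Collection, add to the day-28 call questions on readmission and on major or serious events that a parent can report, for example amputation, limb ischaemia or infection needing treatment. Confirm the answers from records where possible. For children still in hospital at day 28, take the same items from the record.

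Keep events that can only be ascertained in hospital, such as extravasation injury, hyperglycaemia and hospital-acquired infection, to the hospital stay, and say so. Report events before and after discharge separately by arm, with the days in hospital beside the inpatient counts so that they can be read against time at risk.

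The cost is a few extra questions on a call already planned and about one eCRF page. The drawback is that post-discharge events would be parent-reported in an open-label trial, which is why confirmation from records and separate reporting are needed.

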### Data Collection

The central study coordination will provide a study booklet for site staff, and perform site visits and regular videoconferencing to ensure high standard study conduct and to discuss any challenges in study progress. The REDCap online database (43), hosted by The University of Queensland, has been setup to capture baseline demographic variables, comorbidities, disease and severity features, pre-defined study outcomes, information on study treatments, and adverse events. The staff at each study site will be trained in completing this electronic case report form (eCRF) and in performing the follow-up questionnaires. Study participants alive at day 28 will be contacted by phone (unless still in hospital) to assess POPC and FSS. Subsequently, the study nurses will contact families ~2 months post randomization by phone to perform the questionnaires by proxy on neurodevelopment, quality of life and functional outcomes–details of the follow-up will be published separately.

Physiological parameters and organ support will be collected upon randomization, then at 1, 6, 12, and 24 h subsequently. We will collect individual components of organ dysfunction and organ support every day until discharged from PICU to calculate pSOFA scores.

### Biobanking

Where parental consent is available, we will obtain 1–2 mL of EDTA blood, 2.5 mL of PAXgene blood, and 1–2 mL of serum as close to enrolment as possible. The samples will be transferred to a biobank using standard operating procedures and will remain stored for anxillary studies on sepsis markers.

### Data Quality and Monitoring

A detailed monitoring plan has been established which guides the data validity checks embedded in REDCap and monitoring by an auditor not involved in entering the study data. Specifically, we will perform primary source data verification in 100% of enrolled patients for key variables such as randomization allocation, commencement of intervention and consent, study treatments, organ support, PICU length of stay, survival status, and reported protocol deviations and adverse events. Furthermore, we will randomly select 10% of patients where a range of other study data will be verified using primary source verification, such as inclusion and exclusion criteria for ineligible patients, baseline data, first 24 h data, demographic data, daily organ dysfunction data, and hospital discharge data. Regular training of study staff and videoconferences with the central study team will be held to observe study conduct.

### Statistical Analysis Plan

#### Sample Size

We define feasibility of recruitment if ≥65% of eligible patients are enrolled. Enrolment of 60 of 80 eligible patients will yield a recruitment rate of 75% with a one-sided lower 95% confidence interval limit of 66%, which would meet our feasibility metric for recruitment rate. We anticipate a recruitment period of 24 months to meet the target sample size of 60 participants; this sample should provide sufficient data on feasibility and safety, and indicate estimates of potential effect size to calculate power for a future full trial.

#### Analysis

Using the Consolidated Standards of Reporting Trials (CONSORT) flow chart (Figure 1) (44) we will report on screened, included, and excluded patients, the number consented, and number of those with consent withdrawn. We will report on the number and proportion of children enrolled through prospective consent in comparison to consent to continue, timing of consent, and investigate the investigator-stated reasons if consent to continue was employed. Descriptive statistics will be used to compare demographics, clinical history and baseline clinical characteristics between the study arms (Supplementary Table 1), however statistical comparisons will not be undertaken. The estimate of the difference between the two study groups and the corresponding 95% confidence interval (CI) will be reported for outcomes relating to feasibility and clinical characteristics (Supplementary Tables 2 and 3). Quantile regression will be used to assess the comparison for continuous outcomes and the test of two proportions for binary outcomes. All analyses will be based on the intention-to-treat principle. All patients who underwent randomization and for whom consent is available are included in the ITT analysis. Protocol violations and major adverse events will be listed separately (Supplementary Table 4). A sensitivity analysis will be undertaken for primary and secondary outcomes, separating the standard care arm into two groups–those not receiving hydrocortisone, and those receiving hydrocortisone. Descriptive statistics only will be presented on the sensitivity analysis (Supplementary Table 5). In addition, we will provide graphs to describe temporal changes in pSOFA, physiological measures (heart rate, systolic blood pressure), serum lactate levels, use of fluid bolus volume (in ml/kg), and Vasopressor-Inotrope-Score (45) comparing the intervention group vs. controls, starting at time of randomization. Given the study sample, and that no stratification is performed, we will not perform other pre-planned subgroup analyses.

We anticipate that <30% of RESPOND PICU study patients will be co-enrolled into a concomitant study investigating early inotropes in sepsis, named RESPOND ED (ACTRN12619000828123). Analyses on RESPOND PICU will not be adjusted for co-enrolment in RESPOND ED given that both are pilot feasibility studies.

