Paediatric septic shock often is a fulminant disease, and affected children deteriorate rapidly (11). Hence, in order to optimize outcomes and prevent irreversible multi-organ damage, future interventions will need to be applied early after presentation. Therapeutic options for children where septic shock persists despite initial resuscitation remain scarce. Current recommendations for treatment of refractory paediatric septic shock include consideration for intravenous hydrocortisone (12). Several large randomized-controlled trials in septic adults have demonstrated earlier reversal of septic shock using treatment with hydrocortisone (13–15). In children, guidelines explicitly state that clinical trial evidence for the role of hydrocortisone in paediatric septic shock remains unclear, however the use of hydrocortisone appears to be very common (16–18). More recently, ascorbic acid (Vitamin C), has been proposed as a sepsis adjunct therapy. Ascorbic acid carries powerful antioxidant properties and *in-vitro* and animal model evidence indicates protective effects on endotoxin-related endothelial damage and organ function (19, 20). Given that thiamine deficiency is associated with high lactate (21) and an increased risk of death (21), a protocol combining hydrocortisone, ascorbic acid, and thiamine (HAT therapy, or so called metabolic resuscitation) has been trialled in adult studies with some reporting mortality benefit (22, 23), while other trials did not observe differences in patient-centred outcomes (24–28). Both thiamine and ascorbic acid carry an excellent safety profile (29). A recent systematic review on metabolic resuscitation (30) identified nine registered RCTs on metabolic resuscitation in adult septic shock, but none in children. Children may be more prone to vitamin C deficiency during sepsis due to comorbidities, malnutrition, a higher metabolic rate, and a higher proportion of patients with a rapidly progressive disease course. A propensity-matched cohort study from the USA reported excellent safety and feasibility of metabolic resuscitation in children with septic shock (31). Adjusted analyses showed decreased 30- and 90-day mortality (*p* < 0.05) in the intervention group compared to hydrocortisone alone and compared to standard care without hydrocortisone.

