#### Standard Care

Patients in the standard treatment arm can receive hydrocortisone only if clinically indicated at the discretion of the attending ICU staff specialist and should be treated as per the standard institutional approach to septic shock management (12, 32).

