### Study Outcomes

In addition to feasibility outcomes, the study will assess clinical outcome measures, and proxy measures of intervention efficacy (Table 2). *Feasibility outcomes* include consent rates, time to intervention, hydrocortisone administration prior to randomization, and post randomization in the control group, and protocol violations. Survival free of organ dysfunction censored at 28 days is defined as the *primary clinical outcome*. The pediatric Sequential Organ Failure Assessment (pSOFA) score will be used to assess presence and degree of organ dysfunction (36). All-cause deaths occurring within 28 days of enrolment will be allocated zero organ dysfunction free days. pSOFA scores will be assessed every day during which a patient is admitted in PICU. In children not requiring ongoing respiratory or renal support post discharge from PICU, and not under palliative care, those discharged from PICU will be assumed to have no organ dysfunction which is aligned with the practice at the participating institutions. PICU free survival, survival free of inotrope support, survival free of multi-organ dysfunction, survival free of acute kidney injury (AKI) (37), mortality, PICU and hospital length of stay represent the *secondary clinical outcome measures*. In addition, study nurses will contact families at 28 days to perform a Pediatric Overall Performance Category (POPC) (38) and Functional Status Score (FSS) assessment (39). As a modification from the POPC “good” category (healthy, alert, and capable of normal age-appropriate activities of daily life; medical and physical problems do not interfere with normal activity), we divided the first POPC category into “good/normal” (no medical conditions), and b) “functionally normal” (requires medication and medical input, normal intellectually and physically, able to do activities without restriction).

**Table 2 T2:** Outcomes assessed.

**Outcome**	**Criterium**	**Definition**
Feasibility of the protocol	Recruitment and compliance with study protocol	• Recruitment rates; including (i) proportion of eligible randomized, and (ii) proportion of eligible consented using prospective consent and consent to continue. • Time to initiation of metabolic resuscitation in the intervention arm • Proportion of patients in each study arm which receive hydrocortisone prior to enrolment • Proportion of patients in the control arm which receive hydrocortisone after enrolment • Protocol violations

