### Significance

This worldwide first trial on metabolic resuscitation in paediatric sepsis will test the feasibility of an intervention showing promise of improving patient-centred outcomes and cost-effective health care delivery. Study sites include several paediatric hospitals across Australia and New Zealand, leveraging off of the ANZICS Paediatric Study Group network.

The study design is informed by the VITAMINS trial (24) and similar several recently published adult RCTs on metabolic resuscitation. While the optimal dosing of metabolic resuscitation, in particular of ascorbic acid, remains uncertain, weight-based dosing schedules were derived from adult studies, considering expert pediatric critical care pharmacist advice. Of note, we recently reviewed the literature on harm related to high dose ascorbic acid in children and identified that the safety of this intervention is very high even at doses superior to those used in this trial (46). Inclusion and exclusion criteria of this pilot study were adapted from adult trials towards pediatric populations, but it is acknowledged that criteria such as cardiomyopathy were not defined in detail to keep the study pragmatic. Limitations include lack of a dedicated hydrocortisone only arm, and hence pre-planned subgroup analyses on children treated with hydrocortisone, vs. controls without hydrocortisone, and vs. intervention with metabolic resuscitation, will be performed.

The interventions are low cost and are based on globally available drugs with excellent safety profiles_._ The study design is pragmatic, and findings will serve to inform the design of a fully powered trial on high dose ascorbic acid, thiamine, and hydrocortisone in children with septic shock.

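### The hydrocortisone analysis divides only the control arm, by discretionary treatment, and is offered in place of a hydrocortisone-only arm; neither control subgroup is comparable with the undivided intervention arm

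*Protocol article*

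**What the plan says.** The Analysis section of the Statistical Analysis Plan states: "A sensitivity analysis will be undertaken for primary and secondary outcomes, separating the standard care arm into two groups". The two groups are "those not receiving hydrocortisone, and those receiving hydrocortisone". The intervention arm is left whole, and no period in which the hydrocortisone must have been given is stated. The section adds: "Descriptive statistics only will be presented on the sensitivity analysis".

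Under Standard Care, the route to hydrocortisone in the control arm is clinical judgement: "Patients in the standard treatment arm can receive hydrocortisone only if clinically indicated at the discretion of the attending ICU staff specialist". The Introduction gives the clinical background: "Current recommendations for treatment of refractory paediatric septic shock include consideration for intravenous hydrocortisone". It also says that trial evidence in children is unclear and that use seems to be very common.

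The Significance section gives the analysis its purpose: "Limitations include lack of a dedicated hydrocortisone only arm, and hence pre-planned subgroup analyses on children treated with hydrocortisone". The comparators follow in the same sentence: controls without hydrocortisone, and the metabolic resuscitation arm.

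Table 2 lists two related feasibility outcomes. One is recorded in both arms: "Proportion of patients in each study arm which receive hydrocortisone prior to enrolment". The other is the proportion of controls given hydrocortisone after enrolment.

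**The concern.** The intervention arm is everyone randomised to it, whatever their severity. Each control subgroup is a selected part of its arm. If hydrocortisone goes mainly to children whose shock persists, the treated controls are sicker than average and the untreated controls less sick. Setting either beside the whole intervention arm compares children who differ before any drug effect.

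A second selection acts through time. A child must live long enough, and stay in shock long enough, to be given hydrocortisone. A child who dies early or recovers early is counted among the untreated.

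The stake is interpretation. The Sample Size section expects the pilot to supply effect-size estimates for a full trial, and the Significance section says the findings will inform that trial's design. A table presented as making up for the missing arm invites the reader to credit or discredit the vitamins over hydrocortisone alone, which these groups cannot show.

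**Working it through.** The plan gives no figure for this analysis: no expected rate of hydrocortisone use in controls and no severity contrast. There is nothing to reproduce, so the check is an illustration of how large the artefact could be.

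**Inputs from the article**
- 60 children randomised 1:1, so about 30 controls.
- Mortality of septic shock around 17% (Introduction).

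**Assumptions, not in the article**
- No drug has any effect, so expected mortality is 17% in each randomised arm.
- Share f of controls given hydrocortisone: 30%, 50% or 70%, which gives subgroups of 9 to 21 children.
- Severity s is standard normal. Logit P(death) = a + s, with a set so that the mean is 17%.
- Logit P(hydrocortisone) = c + k·s, with c set so that the mean is f, and k = 0.5, 1.0 or 1.5.

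**Method 1, severity model.** Mortality in treated controls is E[P(death)·P(hydrocortisone)]/f. In untreated controls it is E[P(death)·(1 − P(hydrocortisone))]/(1 − f).

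| f | k | Treated controls | Untreated controls | Intervention arm looks better than treated by | Looks worse than untreated by |
|---|---|---|---|---|---|
| 30% | 0.5 | 21.3% | 15.1% | 4.3 | 1.9 |
| 30% | 1.0 | 24.9% | 13.6% | 7.9 | 3.4 |
| 30% | 1.5 | 27.4% | 12.6% | 10.4 | 4.4 |
| 50% | 0.5 | 19.9% | 14.1% | 2.9 | 2.9 |
| 50% | 1.0 | 22.1% | 11.9% | 5.1 | 5.1 |
| 50% | 1.5 | 23.5% | 10.5% | 6.5 | 6.5 |
| 70% | 0.5 | 18.7% | 13.1% | 1.7 | 3.9 |
| 70% | 1.0 | 19.9% | 10.3% | 2.9 | 6.7 |
| 70% | 1.5 | 20.6% | 8.6% | 3.6 | 8.4 |

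The last two columns are percentage points against 17%. The apparent benefit is about 2 to 10 points and the apparent harm about 2 to 8 points, with no true effect.

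**Method 2, direct odds ratio.** Fix the odds ratio of death (treated versus untreated controls) due to severity alone, and solve f·p1 + (1 − f)·p0 = 0.17. With f = 50% and an odds ratio of 3, p1 = 24.3% and p0 = 9.7%, a shift of 7.3 points each way. Over f = 30–70% and odds ratios of 2 to 5, the apparent benefit is 2.6 to 17.5 points and the apparent harm 3.1 to 11.7. With an odds ratio of 1 (no selection) both are zero.

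**Primary clinical outcome.** A simulation on the severity model also assumed that organ dysfunction lasts longer in sicker children. It gave median organ-dysfunction-free days of 18–21 in treated controls, 22–23 or 24 in untreated controls and 22 in the intervention arm, again with no drug effect.

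**Early death.** The models above leave this out. Take f = 50% and k = 1.0. Expected deaths are 15 × 0.221 = 3.3 in treated controls and 15 × 0.119 = 1.8 in untreated controls. If one child who would have been treated dies first, that child is counted as untreated. The rates become 2.3/14 = 16.4% and 2.8/16 = 17.5%. One such death removes the severity contrast, so its net direction cannot be predicted.

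**Against chance.** For 22% of 15 versus 17% of 30, the standard error of the difference is √(0.22·0.78/15 + 0.17·0.83/30) = 0.127, or about 13 points.

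**The case against.** The strongest reply is that the table is descriptive, the article openly names the missing arm as a limitation, and the main comparison is by intention to treat with confidence intervals and is untouched. With a standard error near 13 points, a shift of a few points would hardly be visible. Clinicians may also give hydrocortisone from habit rather than for severity, since the Introduction calls its use very common.

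Much of this stands. The randomised comparison is unaffected. Selection by severity is plausible from the Introduction and Standard Care sections but not established, and the sizes above rest on assumed rates and slopes. What does not stand is that descriptive reporting cures the problem. A median or proportion from a selected group is biased whether or not a test is attached, and the Significance section gives these figures a purpose that they cannot serve.

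A reader might infer that the Analysis and Significance sections contradict each other, one planning a sensitivity analysis and excluding subgroup analyses, the other planning them. The text does not support that. The Analysis section excludes only other pre-planned subgroup analyses, directly after describing the hydrocortisone split, and the groups match. Only the label differs.

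A reader might also take it as fixed that the split uses hydrocortisone given after randomisation. The Standard Care section makes that the natural reading, but the Analysis section states no window, Table 2 records use both before and after enrolment, and the supplementary table for this analysis is not shown.

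**Conclusion.** The concern holds in this form. The article splits one arm only, by a treatment given at clinicians' discretion, and offers the comparison with the undivided other arm as its response to having no hydrocortisone-only arm. Neither control subgroup is comparable with the intervention arm, and the design cannot separate the effect of the vitamins from that of hydrocortisone.

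Selection by severity alone would produce a spurious shift of about 2 to 10 points of mortality if 30–70% of controls are treated, in opposite directions for the two subgroups. That rests on the assumed severity model. A firm claim that the analysis will flatter metabolic resuscitation against hydrocortisone goes too far, because early death before treatment acts the other way and the documents give no rates. The net size and direction are uncertain.

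This is a matter of interpretation in a secondary, descriptive analysis of a pilot. It should be corrected, but it is not a failure of the main analysis.

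**What to change.** 1. Add a descriptive comparison of both arms within strata of hydrocortisone use before randomisation. This is a baseline characteristic that Table 2 already records in each arm, so within each stratum the comparison remains randomised.
2. If the control-arm split is kept, define its time window. Label it non-randomised and exploratory, present it only as a description of contamination in the control arm, and do not set it against the intervention arm. Deleting it is optional.
3. Reword the Significance section to say that the design cannot separate the effect of the vitamins from that of hydrocortisone, and drop the suggestion that the split makes up for the missing arm.
4. Use one label for the analysis in the Analysis and Significance sections.

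The cost is one table shell and some wording, with no new data. The strata will be small and the results will remain descriptive. The baseline strata do not replace the missing arm either.
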